### 3.2. Therapeutic Intervention

Two therapeutic methods will be conducted separately with the same curation frequency and period. Unlike the educational intervention, the therapeutic intervention will cover music therapy and flotation-REST therapy to provide deeper relaxation by offering a more creative environment for participants to engage in symbolic therapeutic activities, such as sensory isolation, to reduce stress and other negative expressions. Although face-to-face conditions may also occur in the two therapeutic groups, we explored the therapeutic effects of music or lying on sand rather than face-to-face communication.

Music therapy (group 4): This therapy involves three parts: A Type I song, a therapeutic song, and a Type II song. Type I is also known as a welcome song, and will be mainly used to activate the patient’s cognitive areas and stimulate recent memories with a relatively slow rhythm. Classical or romantic pieces are usually selected for this period, which lasts for 2–4 min. The therapeutic song will be selected depending on the patient’s interests. For the last part, a progressively faster piece compared with a Type I song will be selected (above 80 bpm). Furthermore, this period would involve lyrics to stimulate the patient’s social and emotional behaviors, including self-esteem. The three musical parts maintain a consistent same volume of 50 decibels [24,25].

Flotation-REST therapy (group 5): This therapy will be conducted by an individual in a soundproof, lightproof, and temperature-controlled (35° Celsius) environment to minimize sensory signals. We need a flotation tank with reverse osmosis water saturated with Epsom salt (magnesium sulfate) to ensure that the whole body is soaked and floats. During the treatment, patients are instructed to lie horizontally and face-up to deepen their relaxation. Notably, a one-week adjustment would be provided considering female patients’ menstrual cycle periods [26,27].

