## 3. Psychological Intervention

### 3.1. Educational Intervention

The participants will receive different psychoeducation programs according to their allocation. All subgroups will receive treatment, including cognitive behavioral therapy and progressive muscle relaxation intervention, during the program [11]. Each session will last for 20–30 min, and the patients will receive a semi-structured dialogue together with brief written advice (BWA) adjusted according to their contemporary situation [12]; furthermore, positive feedback will be provided after each treatment [13]. One session will be conducted per week for six weeks, and the whole evaluation process will last for 3–6 months, with assessments covered in every follow-up. Inpatient therapy will be conducted during patients’ stay at the hospital, while for patients after discharge, therapy will be conducted through at-home training or outpatient sessions [14,15,16]. The purpose of the whole intervention is to achieve emotional relief and self-relaxation.

The educational program will be conducted face-to-face (Group 2) or by telephone (Group 3) according to the participant’s actual condition, including transportation inconveniences. Before the psychological intervention, stretching exercises will be conducted for relaxation in all subgroups [13]. The psychoeducation contents in each group will be much the same, with a semi-structured dialogue given by the nurses or physiotherapists, with necessary guidance and contents, including patient experience sharing, situation sharing that may cause depression and stress, information sharing, problem-solving, skill training, etc. This ensures dialogue completeness, with roughly the same contents and consistency for each group [12,17,18]. In particular, information about pain and sleep management skills; advice on gradual build-up activities, as well as the pace and consistency of activity; and explanations of rest and conditioning will be provided in detail [19,20].

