### 4.4. Adverse Events, Medication Usage, and Co-Interventions

Adverse events and medication use will be recorded along with the follow-up process at pre-operation, and at 1, 3, and 6 months after surgery by stages. Physical activities in all subgroups will be recorded each week after timely treatment. In addition, any other special circumstances, including necessary medication usage and co-interventions (intensity, frequency, and type), will be collected and immediately recorded.

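### Section 4.4 schedules postoperative adverse-event recording at 1, 3 and 6 months, although the interventions, including whole-body flotation, are given weekly and a weekly record already exists

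*Protocol article*

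**What the plan says.** **Schedule.** Section 3.1 of the protocol article states: "One session will be conducted per week for six weeks, and the whole evaluation process will last for 3–6 months". It also states: "Each session will last for 20–30 min". Section 3.2 says that music and flotation are run separately with an equal frequency and period. No section gives the postoperative day of session one.

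**Flotation (Group 5).** Section 3.2 specifies a tank of water saturated with magnesium sulfate, "to ensure that the whole body is soaked and floats".

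**Adverse events.** Section 4.4: "Adverse events and medication use will be recorded along with the follow-up process at pre-operation, and at 1, 3, and 6 months after surgery". The same paragraph has physical activity recorded every week in all subgroups. It then asks for any other special circumstances, with medication and co-interventions as its examples, to be recorded at once.

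**Related passages.**
- Section 3.1, on setting: "Inpatient therapy will be conducted during patients’ stay at the hospital", with home training or outpatient sessions after discharge.
- Section 3.2, on the medium: "we explored the therapeutic effects of music or lying on sand rather than face-to-face communication".
- Section 3.2, under Group 5 only: "a one-week adjustment would be provided considering female patients’ menstrual cycle periods".
- Section 2.2 excludes participants who have a contraindication to the specific therapeutic programme. The contraindications are not listed.
- Section 2.6 places partial weight bearing with crutches and braces after two weeks.

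**The concern.** Exposure is weekly, while the scheduled safety record is at first monthly and then two to three months apart. A problem that arises between two records, such as a wound problem or a reaction during a session, depends on the patient's recall at the next visit or on someone choosing to note it.

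Spontaneous noting may differ between arms. Contact differs by design: telephone, face-to-face, music, tank, or traditional rehabilitation. Section 2.4 states that patients and physiotherapists are not blinded. A comparison of adverse events across five groups is easier to defend if each group is asked the same question equally often.

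The plan already has a weekly record, so a more frequent safety question needs no new visit.

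**Working it through.** The plan gives no figure of its own for this point. Its arm size, the only related figure, reproduces: 34 / (1 − 0.15) = 40 per group, and 5 × 40 = 200.

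**Inputs**
- Six sessions, one per week (section 3.1). Applying this to Group 5 assumes that the equal frequency and period in section 3.2 means the schedule of section 3.1.
- Scheduled postoperative adverse-event records at 1, 3 and 6 months (section 4.4), taken as day 30, day 91 (13 weeks) and day 182 (26 weeks).
- Day of session one after surgery, s: not stated. It is varied from 1 to 28.

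**Formulas**
- Session k falls on day s + 7(k − 1), so session six falls on day s + 35.
- Sessions at or before day 30 = floor((30 − s)/7) + 1.
- Wait from session one to the 1-month record = 30 − s days.
- Wait from session six to the 3-month record = 91 − (s + 35) = 56 − s days.

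| Start day s | Sessions by day 30 | Session one to 1-month record | Day of session six | Session six to 3-month record |
|---|---|---|---|---|
| 1 | 5 | 29 days | 36 | 55 days (7.9 weeks) |
| 3 | 4 | 27 days | 38 | 53 days (7.6 weeks) |
| 7 | 4 | 23 days | 42 | 49 days (7.0 weeks) |
| 14 | 3 | 16 days | 49 | 42 days (6.0 weeks) |
| 21 | 2 | 9 days | 56 | 35 days (5.0 weeks) |
| 28 | 1 | 2 days | 63 | 28 days (4.0 weeks) |

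For starts within two weeks, 3 to 5 of the six sessions come before or at the first scheduled postoperative record, and the wait after session six is about 6 to 8 weeks. With a later start the first gap shrinks, but at least 4 weeks remain after session six.

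**Check on the primary endpoint.** Take the latest start above and one one-week adjustment: session six falls on day 63 + 7 = 70. The 6-month assessment is then 182 − 70 = 112 days (16 weeks) away. An adjustment moves a session by 7 days; nothing in the text cancels one.

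**Check on the immediate-recording sentence.** It follows the sentences on adverse events and on physical activity and speaks of other circumstances. Read as written, adverse events belong to the scheduled times, and immediate recording applies to something else.

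**The case against.** **Safety detail usually sits in the full protocol.** A journal article need not set out reporting procedures, and their absence would be no finding. That stands for the procedures. Section 4.4, however, does not leave the timing open: it names the times.

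**Events may be noted anyway.** Staff meet patients weekly and special circumstances are recorded immediately, so the waits above are upper limits on delay, not expected delays. That also stands. But the sentence does not name adverse events, and informal noting need not be equal between arms.

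**The scheduled record is the same in every arm.** Correct. No differential bias in the scheduled record is shown.

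Three stronger readings are tempting, and the documents do not support them:

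- *That Group 5 is immersed in hospital within days of surgery.* The inpatient sentence is in section 3.1, on the educational intervention, and section 3.2 carries over frequency and period, not setting or start day. The text permits an in-hospital start without stating one. The stated aim of treating persistent postoperative symptoms points to a later start, and the contraindication exclusion in section 2.2 may apply. Section 2.6 does not mention flotation, so its two-week step does not contradict it.
- *That the menstrual adjustment lowers the dose in Group 5.* It shifts timing for some women in one arm. The article does not say that a session is lost.
- *That the 6-month primary comparison is biased.* Under the start days examined, the course ends months earlier.

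The mention of sand is a wording slip beside a full tank specification and is unlikely to mislead a site. Outpatient sessions can supply a tank, so the home option is not a contradiction in itself.

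**Conclusion.** The point holds as a cheap improvement to safety ascertainment. Section 4.4 ties adverse events to the pre-operative record and to 1, 3 and 6 months, while exposure is weekly, and no other provision there names adverse events. If sessions begin within about two weeks of surgery, 3 to 5 of the six would come before or at the first scheduled postoperative record, and an event after session six could wait about 6 to 8 weeks. These figures rest on the assumed start day, on weekly sessions without interruption, and on section 3.2 meaning the schedule of section 3.1. The gap concerns all arms that receive weekly sessions; flotation, with about 40 of the 200 patients, is the arm where wound problems come most readily to mind.

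The remaining inconsistencies about flotation are points of wording that the sponsor should reconcile. They do not establish a safety failure, a loss of sessions or a confounded primary comparison.

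**What to change.** In section 4.4, add an adverse-event question, including wound problems, to the weekly record, and ask it in the same form in all five groups. Say expressly that the control group is included, since the current text says only all subgroups. State how long the weekly record runs, because this decides how far the gap after session six is closed. Keep the records at 1, 3 and 6 months. The cost is one more item on an existing form.

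Separately, the sponsor should reconcile:
- sections 2.2, 2.6, 3.1 and 3.2 on where flotation is given and when it takes place relative to surgery;
- the mention of sand and the water tank within section 3.2;
- the one-week adjustment given only for Group 5 and the statement of equal frequency and period.

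These are decisions for the sponsor. No start rule and no rule for making up sessions is proposed here. The cost is a wording change.

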### 3.3. Control

Patients in this group will receive a traditional rehabilitation program performed by therapists and will adhere to the therapeutic protocol as much as possible. Problems and issues will be solved simultaneously through discussion. In addition, the standardized, structured treatment will be recorded by researchers that have not participated in other parts of the research.

## 4. Measures

### 4.1. Outcome Measures

The modified Harris Hip Score (*mHHS*) contains eight items affiliated with three domains representing clinical aspects, including pain and functional grade (gait, activities, etc.). The mHHS will be scored from 0 (worst functional outcome and maximum pain) to 100 points (best functional outcome and least pain) for each item in the arbitrary weight. Patients with a score of <70 represent a poor result, while a score between 70 and 79 refers to a fair result, a score between 80 and 89 is good, and an excellent result requires a total score over 90 [28,29]. This measurement is used to assess the relationship between physical function and psychological conditions after hip arthroscopy, providing a high construct validity for evaluating bodily pain.

The depression, anxiety, and stress scale (DASS-21 scale) is a self-reported 21-item scale, with subscales, including depression, anxiety, and stress. Each subscale contains seven items, and each is scored from 0 (did not apply to me at all) to 3 (applies to me very much or most of the time). The final score is determined by the total sum of each item, which is subsequently multiplied by 2. For each subscale, scores over 9 represent an indication of depression, a score of 7 indicates anxiety and a score of 14 indicates stress symptoms. Traditionally, the higher the final scores, the more severe the patient’s symptoms will be [30,31,32]. Based on its low cost and ease of administering, as well as providing a higher precision for elderly patients together with reliability and validity, this questionnaire will be used to assess the subjective depressive, stress, and anxiety complaints of participants, as well as their frequency and severity [33].

Patient Health Questionnaire-9 (PHQ-9): The PHQ, which is usually used as a cutoff for diagnosis, will be developed to diagnose depressive disorders, as well as the severity of depression, through the filling out of a questionnaire containing nine items. Each item is rated on a 4-point scale, with ranges from 0 (not at all) to 3 (nearly every day). As the most used clinical diagnosis measurement, a total of 27 is possible, with higher scores illustrating a higher likelihood of severe depressive disorder symptoms [34,35]. The aspects in this questionnaire are mainly correlated to the patient’s psychosocial characteristics, cultural background, and contributing postsurgery symptoms, with a reported sensitivity of 83.84% and specificity of 97.01%, as well as a Cronbach’s α of 0.88 reported in a Norwegian-speaking community sample [36,37].

Huaxi Emotional-distress Index (HEI): The HEI is mainly used as an assessment tool for the rapid screening of inpatients’ psychological status. It covers 11 items for evaluations of depressive or anxious emotions. Each item corresponds to 4 points for the first 10 items, with effects from 0 (no influence) to 4 (severe influence). Scores below 8 indicate normal, scores above 8 indicate negative emotions, and specifically for patients who answered item 9 with 2 or above, reality verification or an assessment of suicidal thoughts may be required. If the total of the first 9 items is above 8, then continue covering items 10 and 11; otherwise, the evaluation is ended. The HEI scale is suitable for localized patient conditions, with a reported validity and reliability of 0.898 and 0.878, respectively [38,39,40,41].

As for each re-assessment of the rehabilitation process, the 6 min walk test will be taken to evaluate a patient’s walking speed, balance, coordination, and ability to perform daily activities. The detailed assessments are listed below in Table 1.

### 4.2. Adherence to the Traditional Rehabilitation Program Group

The number of visits will be recorded after treatment, together with frequency, intensity, time, training type and volume, and exercise progression, both at the ward and at home. Numeric rating scales (0 refers to not at all and 10 refers to completely as instructed) will be used to evaluate the overall adherence to the whole program, with separate components according to specific items.

### 4.3. Relative Hospitalization Cost Assessment

The relative hospitalization cost includes participant hospitalization, outpatient treatment during follow-ups, medication usage, and health services. The aim of this assessment is to determine which intervention is cost-effective for treatment.

### 4.4. Adverse Events, Medication Usage, and Co-Interventions

Adverse events and medication use will be recorded along with the follow-up process at pre-operation, and at 1, 3, and 6 months after surgery by stages. Physical activities in all subgroups will be recorded each week after timely treatment. In addition, any other special circumstances, including necessary medication usage and co-interventions (intensity, frequency, and type), will be collected and immediately recorded.

### 4.5. Sample Size

The primary endpoint will be altered from baseline to 6 months post-surgery in the mHHS scale. A pilot trial was conducted, and the baseline suggested the targeted patients’ population, with a mean mHHS of 85.1 and an SD of 8.7. The minimal clinically important difference (MCID) for the mHHS scale in this population is 8 points [29,42]. Therefore, the sample size of this study will be calculated based on the mHHS SD of 8.7 and the MCID of 8.

G*power software (version 3.1.9.7 for Windows XP, Vista, Germany) was used to calculate the sample size, with an effect size of 0.8 and power of 90%, and a sample size of 34 in each group is required for the minimum inclusion. Considering the allowance of 15% for a loss of follow-up for 12 months postoperatively, 40 participants will be recruited in each group.

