## Abstract

Purpose: The purpose of this protocol was to discover the connection between patients with non-surgical pain or other discomfort and their psychosocial status. Cognitive behavior therapy will be used, which we verified will determine the effect and feasibility of postoperative rehabilitation processes. Materials and Methods: This study will include 200 patients ranging from 18 to 60 years old who have underwent or will undergo FAI arthroscopy in the West China Hospital Sports Medicine Center from 2023 to 2026. A standardized prospective single-center parallel-group randomized controlled trial will be used for these participants. The participants will be divided into intervention (telephone versus face-to-face versus music versus floatation) and control groups. The follow-up periods will be measured pre-operatively, as well as postoperatively at 1, 3, and 6 months. The primary outcomes will include the modified Harris Hip Score (mHHS) and the Visual Analogic Score (VAS), and the secondary outcomes will include the range of motion (ROM), the Huaxi Emotional-distress Index (HEI), and the depression, anxiety, and stress scale (DASS-21 scale). Furthermore, the Patient Health Questionnaire-9 (PHQ-9) and a Short-Form 12 (SF-12) questionnaire will also be evaluated. Discussion: This study will evaluate the clinical and cost-effectiveness of different types of psychosocial-therapy-based rehabilitation methods designed to improve the quality of life of FAI patients with persistent symptoms.

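### The effect size of 0.8 does not follow from the SD of 8.7 and MCID of 8 on which the sample size is said to rest (8/8.7 = 0.92), and the attrition allowance is for 12 months in a trial that ends at 6

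*Protocol article*

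**What the plan says.** Section 4.5 of the protocol article gives the sample-size argument in two paragraphs.

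- **Endpoint:** change in mHHS to 6 months ("The primary endpoint will be altered from baseline to 6 months post-surgery in the mHHS scale").
- **SD:** the pilot described the target population at baseline "with a mean mHHS of 85.1 and an SD of 8.7".
- **Target difference:** "The minimal clinically important difference (MCID) for the mHHS scale in this population is 8 points".
- **Declared basis:** "the sample size of this study will be calculated based on the mHHS SD of 8.7 and the MCID of 8".
- **Calculation reported:** a G*Power run "with an effect size of 0.8 and power of 90%, and a sample size of 34 in each group is required".
- **Attrition:** "Considering the allowance of 15% for a loss of follow-up for 12 months postoperatively", which leads to 40 recruited per group.

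Section 2.3 describes five groups of roughly equal size, and the Abstract gives a total of 200. On timing, the Abstract says "The follow-up periods will be measured pre-operatively, as well as postoperatively at 1, 3, and 6 months". Section 4.4 uses the same schedule, and the last assessment in Table 1 is T3 at 6 months.

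**The concern.** The declared basis and the reported effect size stand in adjacent paragraphs and disagree. A difference of 8 over an SD of 8.7 is 0.92, which no rounding turns into 0.8. A reader therefore cannot tell whether the trial is sized for 8 points, for about 7 points, or for 8 points with a larger SD than the one printed. This bears on how the result is read, because the size of effect that a null finding makes unlikely depends on which of these was meant.

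The attrition sentence has a similar fault. It refers to a 12-month period, and no 12-month visit of this trial appears in the article. The other mentions of 12 months, in the Introduction and Discussion, concern earlier studies.

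**Working it through.** **Inputs.** SD 8.7, MCID 8, effect size 0.8, power 90%, 34 and 40 per group, and 15% loss come from section 4.5. Alpha 0.05 comes from section 4.6. The article does not name the sizing test or its sidedness. I used a two-sample t-test (noncentral t) with equal groups. The two-sided version reproduces the stated figure; the one-sided version gives 27.5, so 28 per group, and does not.

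**1. Reproduce the plan's figure.** With d = 0.8, two-sided alpha 0.05 and power 0.90, the required n is 33.83, so 34 per group (power at 34: 90.2%). Attrition: 34 / (1 − 0.15) = 40. Total: 5 × 40 = 200. The chain from 0.8 to 34 to 40 to 200 is correct.

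**2. Effect size from the stated basis.** d = difference / SD = 8 / 8.7 = 0.9195, or 0.92.

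**3. Sample size from the stated basis.** With d = 0.9195 and the same test, alpha and power, n is 25.85, so 26 per group (power at 26: 90.2%). Attrition: 26 / 0.85 = 30.6, so 31. Five groups: 5 × 31 = 155.

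**4. What 0.8 implies.**
- At SD 8.7: difference = 0.8 × 8.7 = 6.96 points.
- For 8 points: SD = 8 / 0.8 = 10.

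The article states neither figure.

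**5. Power at 34 evaluable per group, one unadjusted comparison.**

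| Effect size | Power |
|---|---|
| 0.80 | 90.2% |
| 0.92 | 96.2% |

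**6. Dependence on the SD.** The 8.7 is a baseline SD, while the endpoint is a change. If the SD is 8.7 at both times and the baseline-to-6-month correlation is r, the SD of change is 8.7 × √(2(1 − r)). The article gives no r, so the values below are assumptions. They use an 8-point difference and 34 per group.

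| r | SD of change | d | Power |
|---|---|---|---|
| 0.30 | 10.29 | 0.78 | 88% |
| 0.34 | 10.00 | 0.80 | 90% |
| 0.50 | 8.70 | 0.92 | 96% |
| 0.60 | 7.78 | 1.03 | 99% |

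The SD of change equals 8.7 only at r = 0.5, and it reaches the 10 that would justify 0.8 at r of about 0.34.

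**7. Attrition period.** The endpoint in section 4.5, the Abstract, section 4.4 and Table 1 all end at 6 months; only the attrition sentence says 12. The label does not enter the arithmetic, since 34 / 0.85 = 40 under either period.

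**The case against.** The best defence is that the reported calculation is internally right and the discrepancy lies on the safe side. Since 0.8 is smaller than 0.92, the trial recruits more than its named inputs require for one two-group comparison, and 0.8 is printed openly. All of that stands. A reader who sees a wrong effect size might infer that the trial is underpowered or that enrolment must change. The article supports neither inference.

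A second defence is that 0.8 may reflect the SD of the change score, which would be about 10 at a correlation near 0.34. This is possible, and it is a good reason not to assume that 0.92 is the true value. It does not rescue the text, which names 8.7 as the basis and gives neither a change-score SD nor a correlation.

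A third is that an article condenses a fuller document. That would excuse an omission, such as the unnamed test. Here, though, printed figures disagree with each other, and so do 6 and 12 months.

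It is also tempting to say that the spare margin covers multiplicity across the five arms, and to quote a power after adjustment. The article names no comparison family, and the answer changes with the one chosen, so no adjusted figure belongs in this point.

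**Conclusion.** The point holds as an inconsistency in the sample-size statement. The declared inputs give d = 0.92 and 26 per group, or 31 with 15% loss. The reported effect size of 0.8 gives 34 and 40. SD 8.7, a difference of 8, 90% power and a minimum of 34 cannot all be true together. The gap is 8 evaluable patients per group, or 200 against 155 recruited in total.

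The error is conservative for a single two-group comparison, where 34 per group gives about 96% power. That figure rests on a two-sided 0.05 t-test without adjustment and on 8.7 being the SD of the analysed endpoint, which the article does not establish.

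The attrition period contradicts the 6-month design but does not alter the 40 per group. The article does not show whether 15% was meant for 6 or for 12 months, so it cannot be said that the allowance is too small or too large. The matter should be corrected, but it does not endanger the trial.

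**What to change.** Keep 34 evaluable and 40 recruited per arm, and make the statement consistent in one of two ways.

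1. Keep 0.8 and state the target difference and SD that produce it: about 7 points at SD 8.7, or 8 points at SD 10. If the SD of 10 is a change-score SD, give the correlation assumed and its source.
2. Restate the effect size as 8/8.7 = 0.92 and give the power that 34 per group provides (about 96%). Label it as conditional on 8.7 being the SD of the analysed endpoint and on a single unadjusted comparison.

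The sponsor should choose according to how 0.8 was actually obtained. No multiplicity-adjusted power should be inserted unless the comparison family is defined first.

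For attrition, align the period with the 6-month endpoint and confirm that 15% is the intended allowance for that period, rather than only changing the number of months.

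The cost is a few sentences in section 4.5, with no change to enrolment, endpoint or analysis.
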